## What is already known

Delirium screening using the usual paper version assessment tool by nurses has no effect on clinical outcomes.Clinical decision assessment systems have been demonstrated to improve patients’ adherence and clinical outcomes.No high-quality evidence exists on the effectiveness of a 3D-DST in improving outcomes of older adults compared to the usual paper version.

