## Introduction

Delirium is a common neurocognitive syndrome in hospitalized older adults with fluctuating symptoms [1, 2]. The incidence of delirium in hospitalized older adults has been reported to be 10% ~ 40% in different settings [3–6]. Delirium during hospitalization will increase the risk of falls, decrease cognitive function, aggravate frailty, and increase mortality in older adults [1, 7]. The severity of adverse effects was positively correlated with the severity and duration of delirium [8]. Prompt recognition of delirium is the first key step in its proper management.

Relevant guidelines for the routine assessment and management of delirium have been issued [9, 10], and several studies have found that delirium assessment combined with multi-component intervention can effectively improve clinical outcomes of patients [11, 12]. However, the majority of patients are not routinely monitored for delirium, guidelines are poorly implemented and hindering timely prevention and management [13]. The possible reasons for the low adherence to delirium assessment are multiple but mainly due to the implementation barriers, such as the monitoring instrument is not routinely used, the complicated procedure of the evaluation instrument, the long evaluation time required for delirium increases the workload of the nurse, etc. [14–16]. A prospective study also demonstrates that routine delirium detection by bedside nurses using the usual paper version assessment tool does not improve clinical outcomes [17].

Clinical decision assessment systems have been widely used in the medical field and have been demonstrated to improve patients’ adherence and clinical outcomes [18, 19]. We have developed a clinical decision assessment system (3D-DST) based on the 3-min diagnostic interview for CAM-defined delirium (3D-CAM), which is developed for the assessment of delirium in older adults with high sensitivity and specificity [20]. 3D-DST simplified the evaluation process of the 3D-CAM paper version, the usability of 3D-DST is significantly better than that of the paper version when used by bedside nurses, and the assessment time has been shortened by 2.1 min [20]. However, no high quality evidence exists on the effectiveness of 3D-DST in improving delirium identification and clinical outcomes of older adults compared to the usual paper version.

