### Participants

The participants are older patients continuously admitted to four general medical wards. Patients should be: 1) age ≥ 65 years old, 2) able to communicate effectively in Mandarin, 3) stay in the hospital longer than two days. Exclusion criteria are: 1) severe hearing or visual impairment, 2) refuse to participate in this study, 3) continuous coma during the study period, 4) severe dementia which is defined as a diagnosis documented in the medical record because such patients cannot be assessed for delirium. This study was approved by the ethics committee of the Capital Medical University and the study hospital. Patients who meet the inclusion criteria will be informed about the study protocol, and written informed consent will be obtained from the older participant or their legal representatives by the first author. Three supervisors (member of the Ethics Committee, administrators of the research program and education department in the hospital) will monitor the accuracy and feasibility of the research process once a year.

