### Cluster randomization and blinding

Before randomization, the wards that participated in the study will be pair matched according to the specialty. Within each of the two pairs, wards will be randomly assigned (1:1) to the intervention or control group using random numbers generated by the computer, which indicates that each group will contain one neurology and one respiratory ward. The medical staff who will be involved in the study only know the protocol of their ward, but not be aware of the protocol of other wards and the hypothesis of the study. Due to the allocation sequence generating, participants’ enrollment, participants’ assignment, data and outcome collection will be done by a nurse researcher, therefore the protocol will not be blinded to the nurse researcher. However, the nurse researcher and the bedside nurse will be unaware of each other's assessment results of delirium.

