### Sample size

The primary outcome is delirium duration. We expect that the delirium duration of the intervention group will be one day shorter than that of the control group, with a standard deviation of 1.8 [28], α of 0.05, and intraclass correlation coefficient of 0.00001. Our study will be estimated to provide more than 80% power, at least five delirium-positive patients in each group (ward), and 20 delirium-negative patients will be needed. According to our previous study, the incidence of delirium is approximately 10%, with an estimated 10% of patients dropping out during the study, at least 202 older patients will be needed. Patients will be given a detailed explanation of the benefits they will receive from participating in the study to reach the target sample size.

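### Recruitment leans on a promise of benefit that the plan itself calls unestablished; one neutral explanation in all wards and a refusal tally would guard against differential consent

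*Protocol article*

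**What the plan says.** The last sentence of the protocol article's Sample size section reads: "Patients will be given a detailed explanation of the benefits they will receive from participating in the study to reach the target sample size". It gives the content of the message (benefits), presents them as certain, and names the purpose (filling the sample).

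Other sections bear on it:

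- **Evidence for the new tool.** Introduction: "no high quality evidence exists on the effectiveness of 3D-DST in improving delirium identification and clinical outcomes of older adults"; the comparator there is the paper tool. The Abstract says much the same.
- **Evidence for the control tool.** What is already known: "Delirium screening using the usual paper version assessment tool by nurses has no effect on clinical outcomes".
- **Consent.** Participants: "Patients who meet the inclusion criteria will be informed about the study protocol, and written informed consent will be obtained"; the patient or a legal representative may give it.
- **Who recruits.** Cluster randomization and blinding assigns sequence generation, enrolment, assignment and outcome collection to a nurse researcher, and concludes: "therefore the protocol will not be blinded to the nurse researcher".
- **What staff know.** The same section says that ward staff "only know the protocol of their ward, but not be aware of the protocol of other wards and the hypothesis of the study".
- **Shared care.** Delirium prevention and treatment supplies one set of interventions to both arms. Adherence/termination says that the researchers will not act on staff adherence, and Study outcomes lists that adherence as a secondary outcome.

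**The concern.** A trial done because benefit is uncertain should not recruit by presenting benefit as certain. Participants are aged 65 or over, and some consent through a representative, so balanced information matters in its own right.

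The statistical interest lies in the cluster design. When wards are randomised first and patients are asked for consent afterwards, randomisation does not protect the composition of the arms against differences in who agrees. The risk grows if the person recruiting knows the ward's arm and the message is about benefit. With two wards per arm, an imbalance of this kind would not be expected to average out.

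A second possible route concerns staff. Adherence to assessment, prevention and treatment is measured, and the plan wants ward staff unaware of the hypothesis. An account of expected benefit given to inpatients and their families could reach the nurses who look after them.

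**Working it through.** The plan gives no figure for consent or refusal, so there is nothing to reproduce. The check sets the sections side by side.

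**1. Is there a benefit that patients can be sure of receiving?** There are three candidates.

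- *The 3D-DST, in the intervention wards.* The Abstract, What is already known and the Introduction all say that high-quality evidence of better outcomes than with the paper version is lacking. Its superiority is the trial hypothesis.
- *Nurse screening with the paper tool, in the control wards.* What is already known reports no effect on clinical outcomes.
- *Assessment together with the prevention and treatment package, in both arms.* The Introduction does say that assessment combined with multi-component intervention can improve outcomes. But the package is handed to head nurses on paper, the researchers do not influence its uptake, and uptake is an outcome. Its delivery to a given patient is therefore not assured.

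A possible benefit exists in both arms under the third candidate. A certain one exists under none.

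**2. Is the arm known when the patient is approached?** The Delirium assessment section has nurses trained separately by arm before the study begins, so ward allocation precedes enrolment. The nurse researcher who enrols also handles allocation and is not blinded. The Participants section assigns written consent to the first author; the article does not say whether this is the same person. The conditions for arm-dependent recruitment are present.

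**3. Does the article say that the message differs by arm or reaches staff?** No. It does not name the benefits, does not vary them by ward, and describes no disclosure to nurses. Both routes are possibilities that follow from steps 1 and 2.

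**4. Would differential consent be visible?** Refusal is one of the exclusion criteria, so patients who refuse leave before the analysis set is formed. Only a count of patients approached and refusing, by ward, would show a difference.

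**5. Size.** This can be illustrated only with assumed consent rates. The target of 202 at 1:1 gives 202/2 = 101 per arm. Approaches needed = 101 / agreement rate.

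| Assumed agreement rate | Approached per arm | Refusing per arm |
|---|---|---|
| 80% | 101/0.80 ≈ 126 | ≈ 25 |
| 65% | 101/0.65 ≈ 155 | ≈ 54 |

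If both arms had the same rate, they would be equally selected on this measure. At 80% in one arm and 65% in the other they would differ by 15 percentage points. Neither rate comes from the article, and nothing in it converts such a difference into days of delirium.

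**The case against.** The strongest reply is that the sentence can be read without contradiction. The evidence gap in the Introduction is a comparison between two tools. Both arms receive twice-daily nurse assessment, the same prevention and treatment interventions, and twice-daily assessment by the nurse researcher. The Introduction cites support for combining assessment with multi-component intervention, so the benefits explained may be those common to all patients. This stands in part: it rules out saying that neither arm offers any benefit. It does not rescue the certainty of the wording, since delivery of the package is not assured.

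A reader might infer that consent is in fact slanted by arm, or that the hypothesis does leak to staff. The article supports neither. Patients are in any case to be informed about the protocol, so conversation between patients and nurses is possible with or without this sentence. Recruitment after allocation likewise comes from the design and would remain if the sentence were deleted.

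Nor is concealment of the hypothesis the only masking measure. Staff are also kept from knowing the other wards' protocols, and the nurse researcher and bedside nurses do not see each other's delirium results.

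Finally, the consent form and full protocol are not shown. They may contain a balanced statement of uncertainty, and the flow diagram, also not shown, may already count refusals. The article therefore does not establish that the consent given was inadequate. The finding rests on what the printed sentence says, which material elsewhere could balance but would not make correct.

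**Conclusion.** The point holds as a low-severity one with a cheap remedy. The sentence makes an explanation of assured benefit a means of reaching the target, while the same article says that the tool's advantage is not established and leaves delivery of the shared care to staff adherence under study. Because an unblinded researcher enrols patients after ward allocation, such a message could lead to differential consent and could weaken concealment of the hypothesis. Both are risks, not shown events.

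No size can be given for the effect on delirium duration. The conclusion assumes that the sentence describes actual recruitment practice, and that ward allocation was known before patients were approached, as the training and blinding sections imply.

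**What to change.** Replace the sentence with one neutral explanation, used word for word in all four wards. It should describe the study and the care given, say that personal benefit is not established, and not state an expected advantage of either tool. It need not hide the tool in use, which would sit badly with the commitment to inform patients about the protocol.

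Record the numbers approached, eligible and refusing, by ward, and report them by ward and arm. Trial status says that recruitment began in September 2020 and was expected to end in November 2023. The new explanation can therefore apply only to patients still to be approached, and the counts should be reconstructed for the earlier period where records allow.

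The cost is rewording with notification to the ethics committee, a simple tally, and possibly slightly slower recruitment.

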### Intervention and implementation

The intervention includes assessment, prevention, and treatment of delirium implemented by nurses and clinicians (Fig. 3).

**Fig. 3 Fig3:**
[figure not shown]
CONSORT flow diagram

#### Delirium assessment

Prior to the study, bedside nurses of the control and intervention groups will be trained respectively. The nurses in the intervention group will perform routine delirium assessments on the included older patients with 3D-DST, while the nurses in the control group will perform daily delirium assessments with the 3D-CAM paper version. The training will include the concept of delirium, clinical manifestations, the training manual of the 3D-DST or 3D-CAM, which will last for 30 min. Due to the characteristic of fluctuating of delirium, enrolled patients will be evaluated for delirium twice a day by bedside nurses during the forenoon and night.

#### Delirium prevention and treatment

Prior to the study, our team summarized prevention and treatment interventions according to the NICE (National Institute for Health and Clinical Excellence) guidance and expert consensus in older patients with postoperative delirium by Chinese and American experts [9, 10, 29]. Based on the clinical situation and discussion with geriatric experts in the participating hospital, the final version of the delirium prevention and treatment interventions are determined. The researcher delivers the paper version of interventions to the head nurses in both the intervention and control groups. The intervention details are as follows (Table 1):A.Prevention: monitoring and managing of hypoxemia, early mobility and/or physical rehabilitation, early mobility and/or physical rehabilitation, pain assessment, and management.B.Treatment: identifing and managing the possible underlying cause, pharmacologic treatments, information and assessment, and interventions for people in whom delirium does not resolve.

**Table 1 Tab1:** Interventions for delirium prevention and treatment

Intervention	Details
Monitoring and management of hypoxemia	Assess for hypoxia and optimize oxygen saturation if necessary
Early mobility and/or physical rehabilitation	Encourage the person to mobilize soon after surgery, walk (provide walking aids if needed-these should be accessible at all times), encourage the person to carry out and active range of motion exercises, even if unable to walk, the intervention of the rehabilitation department
Medication reductions	Reduce the types of drugs you use, avoid medications that induce delirium, use alternative therapies or consult a psychiatrist to adjust dosage (anticholinergic drug, anticonvulsant drug, tricyclic antidepressant, antihistamine drug, antiparkinson drug, antipsychotic drug, benzodiazepines, H2 receptor antagonists, non-benzodiazepine, opioid analgesics)
Pain assessment and management	Optimize postoperative pain control, starting and reviewing appropriate pain management in any person in whom pain is identified or suspected. Preferably with nonopioid pain medications to minimize pain in older adults to prevent delirium
In people diagnosed with delirium, a medical evaluation should be performed to identify and manage underlying contributors to delirium	
Pharmacologic treatments	The prescribing practitioner may use antipsychotics at the lowest effective dose for the shortest possible duration to treat patients who are severely agitated or distressed, and are threatening substantial harm to self and/or others A. Hyperactive delirium: the use of antipsychotics (e.g., haloperidol, risperidone, olanzapine, quetiapine, or ziprasidone) at the lowest effective dose for the shortest possible duration may be considered to treat delirious patients who are severely agitated or distressed or who are threatening substantial harm to self and/or others. Cholinesterase inhibitors should not be newly prescribed to prevent or treat postoperative delirium. Benzodiazepines should not be used as the first-line treatment of agitation associated with delirium. The principles of drug treatment are as follows: a. Monotherapy is better than combination drug therapy b. Start at the lowest clinically appropriate dose and titrate cautiously according to symptoms c. Select drugs with low anticholinergic activity d. Stop medication immediately e. Continued application of nonpharmacologic intervention, identify and manage the possible underlying cause(s) B. Hypoactive delirium: antipsychotics and benzodiazepines should be avoided for treatment of hypoactive delirium C. Mixed delirium: when hyperactive delirium occurs, treated according to the treatment method of hyperactive delirium. When hypoactive delirium occurs, treated according to the treatment method of hypoactive delirium
Information and assessment	Offer information to people who are at risk of delirium or who have delirium, and their family and/or carers. Inform them that delirium is common and usually temporary. Describe people’s experience of delirium. Encourages people at risk and their families and/or carers to tell their healthcare team about any sudden changes or fluctuations in behavior. Encourage the person who has had delirium to share their experience of delirium with the healthcare professional during recovery
For people in whom delirium does not resolve	Re-evaluate for underlying causes. Follow up and assess for possible dementia

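### Table 1 gives two conflicting criteria for considering an antipsychotic, and its stop instruction has no condition attached

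*Protocol article*

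**What the plan says.** The row opens with a general sentence: "The prescribing practitioner may use antipsychotics at the lowest effective dose for the shortest possible duration", and continues "to treat patients who are severely agitated or distressed, and are threatening substantial harm to self and/or others". Item A of the same row, on hyperactive delirium, says that the same drug class may be considered "to treat delirious patients who are severely agitated or distressed or who are threatening substantial harm to self and/or others". The drug principles listed under item A include "b. Start at the lowest clinically appropriate dose and titrate cautiously according to symptoms" and, two lines later, "d. Stop medication immediately".

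The text before Table 1 presents these interventions as settled after discussion with geriatric experts at the hospital. The paper sheet goes to the head nurses of both groups. Pharmacologic treatment is named there as one of the treatment components. Under Study outcomes, adherence to prevention and treatment is a secondary outcome: interventions carried out as a percentage of those that were in theory due. Under Adherence/termination, the researchers say they will not intervene in how staff adhere.

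**The concern.** One table cell describes two different groups of patients for whom an antipsychotic may be considered, and it contains a stop instruction with no stated occasion. Staff who follow the opening sentence and staff who follow item A can reach different decisions about the same patient while both believe they are following the sheet. For older inpatients with delirium, that is a safety reason to make the text consistent. A smaller, secondary issue is how drug use is treated when the adherence rate is reported, because pharmacologic treatment is one of the listed components.

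**Working it through.** The plan states no figure on this point, so there is nothing to reproduce. The check compares the wording.

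**Step 1. Do both sentences apply to the same patients?** For hypoactive delirium the row says that "antipsychotics and benzodiazepines should be avoided for treatment of hypoactive delirium". For mixed delirium it refers staff to the hyperactive or the hypoactive rule, according to the phase. The general sentence and item A therefore meet in hyperactive delirium and in the hyperactive phase of mixed delirium. They are not rules for different populations.

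**Step 2. Do they agree?** Let X = severe agitation or distress, and H = threatened substantial harm. The opening sentence is X AND H. Item A is X OR H.

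| X | H | Opening sentence | Item A | Agree? |
|---|---|---|---|---|
| yes | yes | covered | covered | yes |
| yes | no | not covered | covered | no |
| no | yes | not covered | covered | no |
| no | no | not covered | not covered | yes |

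They differ in 2 of 4 states, or in 2 of the 3 states with at least one condition present. Item A is always the wider. If agitation and distress are counted separately there are 8 states: the opening sentence covers 3 and item A covers 7, so they differ in 7 − 3 = 4.

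**Step 3. Can the stop instruction be applied?** Principle (b) has the dose adjusted to symptoms, and the row asks for use to be as brief as possible. Both assume a period of treatment. Principle (d) gives no event, time or symptom state that ends that period. Starting, titrating and stopping can be successive steps, so (d) need not contradict (b). What is missing is the condition that says when (d) takes effect.

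**Step 4. How many patients could be involved?** These counts are logical states, not patients. At the 10% incidence assumed under Sample size, 202 × 0.10 = about 20 enrolled patients would have delirium. Only those with hyperactive features and exactly one of X and H fall in the gap. The document gives no frequency for that subset, so 20 is a ceiling under the planning assumption and not an estimate.

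**The case against.** The strongest reply is that both sentences only permit. The first says that the prescriber may use the drug; item A says that it "may be considered to treat delirious patients". Neither makes a prescription due, and the opening sentence does not say that it is the only route. Item A could be taken as the specific rule that prevails, leaving little more than untidy duplication. Much of this stands, and it limits what can be claimed. It does not remove the inconsistency: the row does not say that item A prevails, and a reader of the opening sentence alone would apply the narrower description.

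Three stronger readings are tempting, and the document does not support them.

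- **A reader might infer that (b) and (d) flatly contradict each other.** That requires (d) to mean stopping at the moment of starting, which would also cancel the other drug principles. An incomplete instruction is the better description.
- **A reader might infer that adherence cannot be scored.** A permission adds nothing by itself to the interventions that are due, and the other rows of Table 1 can still be scored. Item-level scoring rules may be in the full protocol, which is not shown.
- **A reader might infer bias between the arms.** Both arms receive the same sheet, so the ambiguity is common to both. Nothing shows that whole wards would read it differently or that any split would follow allocation.

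It can also be said that a correction comes late. Recruitment began in September 2020 and was expected to end in November 2023, while the article appeared on 11 September 2023. That is fair, and it governs how earlier patients should be handled.

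**Conclusion.** The point holds as a wording inconsistency in the treatment sheet. The two start sentences conflict for patients with exactly one of the two conditions, and the stop instruction lacks its condition. The conflict follows from the text and needs no numerical assumption. The number of patients affected is unknown, with a ceiling of about 20 if the planned incidence holds. Sample size, power and the definition of delirium duration are untouched, and no effect on the comparison between arms is shown. The correction is worth making because staff in both arms use this sheet and the clarification serves patient safety.

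**What to change.** The study's clinicians should:

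1. Reconcile the opening sentence and item A so that the row states one consistent start criterion.
2. Complete principle (d) with the condition it was meant to carry, so that it can be read together with (b) and the limit on duration.
3. Issue the same corrected sheet to all four wards on one date.

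The content of these rules is for the clinicians to settle. For the analysis, record the date of issue, flag patients treated before it, and do not judge their care against the corrected wording. The report should state whether and how the permissive drug item enters the numerator and denominator of the adherence rate.

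The cost is a short wording amendment, a reissued sheet and a date flag. With recruitment due to end about two months after publication, the new sheet may reach only the last patients. For most of the sample, the practical gain is then a clear account in the report of which wording was in force and how drug use was counted.
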